### 2.4. Functional Ability Tests

A battery of five functional ability tests will be performed, these are as follows:(1)Two-minute walk test. This test requires that all patients walk as far as possible for over 2 min. It is used to assess an individual’s ability to perform activities of daily living independently [22].(2)Timed 25-Foot Walk (T25-FW) test. The test assesses walking speed achieved over a 25-foot distance. It is a validated test that reflects the patient’s mobility and leg function performance [23].(3)Sit-to-stand test (STS). Participants are encouraged to complete five successive full stands from a seated position. The test is used to indicate lower limb strength, balance, and mobility [18,19]. It has been reported that the STS times are associated with standing and leaning balance and mobility in older people. Slow STS times have also been found to predict subsequent disability, falls, and hip fractures [24].(4)Berg Balance Scale (BBS). The BBS evaluates the performance in 14 specific activities that require a balance function (e.g., picking up an object or standing on one leg) necessary for daily living activities. Participants are scored on a 5-point (0–4) ordinal scale depending on their ability to complete the requested actions. A score of 0 is assigned when the task cannot be achieved, and a score of 4 indicates independence. A score of 45 or less indicates a high risk for falls [25].(5)The Mini-BESTest (Balance Evaluation Systems Test) is a streamlined clinical assessment tool designed to evaluate balance impairments in individuals with various conditions, including neurological disorders. It is a condensed version of the original BESTest, aiming to provide a more practical and time-efficient method for clinicians to assess patients’ balance function [26].

### 2.5. Nutrition Assessment

The effectiveness of nutritional education sessions will be conducted by implementing dietary assessment tools and questionnaires. This provides valuable insights into participants’ dietary patterns, nutrient intake, and lifestyle habits. The questionnaires that will be used are provided below:The 7-day food diary is a detailed record where participants log everything they eat and drink over a week. This diary approach allows for a comprehensive analysis of an individual’s food and nutrient intake, capturing day-to-day variations in eating habits.The self-administered, semi-quantitative food frequency questionnaire (FFQ) of 36 items (medium-FFQ); the medium-FFQ is a self-administered questionnaire designed to estimate an individual’s habitual food and nutrient intake over the previous 2–3 months.The 12-item questionnaire on dietary and lifestyle habits. After each biweekly nutrition education session, participants are asked to complete a 12-item questionnaire focusing on their dietary and lifestyle habits during the last week.

### 2.6. Psychological Intervention Evaluation

To evaluate the effectiveness of the psychoeducational program, the following established questionnaires will be used:The Hospital Anxiety and Depression Scale—HADS: The HADS is a widely used instrument designed to detect states of depression and anxiety. It consists of 14 items, divided equally into two subscales: one for anxiety and the other for depression.Perceived Stress Scale—PSS: The PSS measures the degree to which situations in one’s life are appraised as stressful. It is a self-reported questionnaire that assesses the perception of stress over the past month. Items are designed to understand how unpredictable, uncontrollable, and overloaded respondents find their lives.Cognitive Fusion Questionnaire—CFQ-7: The CFQ-7 is a short form of the original Cognitive Fusion Questionnaire. It assesses the extent to which an individual experiences fusion with their thoughts or the degree to which they identify with their thoughts so closely that they are unable to separate themselves from them.Valued Living Questionnaire—VLQ: The VLQ measures the extent to which individuals live according to their values. It consists of two parts: the first part assesses the importance of different value domains (e.g., family, health, education), and the second part evaluates how consistently individuals act in accordance with these values.MPFI Psychological Flexibility subscale: The MPFI assesses an individual’s ability to be in the present moment with full awareness and openness to experiences and to take action guided by their values. This construct is central to acceptance and commitment therapy and is associated with better mental health outcomes.Connor–Davidson Resilience Scale—CDRISC-25: The CD-RISC-25 is a 25-item scale measuring the strength of an individual’s resilience, or their ability to cope with and bounce back from adversity. The scale covers various aspects of resilience, including personal qualities, the positive acceptance of change, and secure relationships.Multiple Sclerosis Quality of Life-54 (MSQOL-54): The MSQOL-54 is an MS-specific quality-of-life instrument that includes generic and MS-specific items. It encompasses 54 items covering a broad range of physical, mental, and social health domains, providing a comprehensive assessment of the quality of life in MS individuals.The patient-determined disability scale (PDDS): The PDDS serves as a valuable self-reported outcome measure for assessing disability. This scale allows patients to provide their perspectives on the impact of MS on their daily functioning, reflecting their unique experiences and challenges [27].

### 2.7. Intervention

This program is structured to provide a holistic, supportive, and adaptable approach to managing MS, focusing on physical health, nutritional balance, psychological support, and practical strategies for daily living (Figure 1). The program includes:

#### 2.7.1. Exercise Intervention and Education

The exercise program included in this intervention has been specifically designed to encourage participants to increase physical activity while reducing sedentary behaviour, thereby promoting behavioural change. Participants will engage in structured exercise sessions that are tailored to promote activity behaviour change, which may include a variety of exercises such as aerobic activities (e.g., walking, cycling), strength training, flexibility exercises, and balance training, depending on the participant’s goals and capabilities. An exercise physiologist will provide regular support and guidance to ensure that participants are on track. The exercise program will include:

Education Sessions: Participants will meet virtually with an exercise physiologist every two weeks via Microsoft Teams 24074.2321.2810.3500. During these sessions, participants will receive personalized education about their specific needs, including exercise techniques, goal setting, overcoming barriers to physical activity, and strategies for increasing daily movement and reducing sedentary time. Furthermore, the exercise physiologist will discuss the benefits of regular exercise. These benefits may include improved cardiovascular health, enhanced muscular strength and endurance, better flexibility and balance, increased energy levels, stress reduction, mood enhancement, weight management, and overall improvement in quality of life. Understanding these benefits will help participants appreciate the importance of incorporating exercise into their daily routine and motivate them to adhere to the program.

Exercise Videos: Weekly, customized exercise videos will be uploaded to the Teams platform for participants to access. These videos will provide guidance on performing exercises safely and effectively, allowing participants to engage in physical activity at their convenience while receiving ongoing support and instruction.

Mobile App Integration: A mobile app will be developed to track and monitor participants’ daily exercise levels. The app will be integrated with Google Health Fit and iOS Health Fit, allowing participants to monitor their progress, set goals, receive reminders easily, and access resources to support their physical activity progress.

The exercise program will be tailored to each participant’s needs, abilities, and preferences. Modifications may be made based on factors such as fitness level, health status, mobility limitations, and personal goals. Throughout the intervention period, participants’ progress will be closely monitored through functional ability tests, including the 2-min walk test, the five-times sit-to-stand test, etc. These tests will be conducted every three weeks to assess participants’ functional abilities and overall improvement. Based on the results of these functional ability tests and ongoing monitoring of participants’ progress, the intensity and content of the exercise program will be adjusted accordingly. If participants demonstrate improvements in their functional ability and overall fitness levels, the exercise physiologists will modify the program to gradually increase the intensity or introduce new exercises to continue challenging them. Conversely, if participants experience difficulties or limitations during the program, modifications will be made to ensure their safety and comfort while promoting progress toward their goals. These modifications may include reducing the intensity of certain exercises, focusing on specific areas of weakness or discomfort, or providing alternative exercises that better suit the individual’s needs.

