### 2.8. Comprehensive Assessment

To monitor progress and adjust the program as needed, participants’ functional ability, nutritional status, psychological condition, and overall quality of life will be evaluated at three key points: baseline (before starting the program), after three months, and upon completion of the program at six months.

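### The two-minute walk and sit-to-stand outcome tests are also run every three weeks inside the Be Cool program, so test familiarity is confounded with treatment on these two secondary measures

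*Protocol article*

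**What the plan says.** The Introduction names functional ability as a secondary outcome on which Be Cool is expected to do better than usual care. Section 2.4 defines how it is measured: "A battery of five functional ability tests will be performed". The first test is the two-minute walk and the third is the sit-to-stand ("Participants are encouraged to complete five successive full stands from a seated position"). The other three are the Timed 25-Foot Walk (T25-FW), the Berg Balance Scale and the Mini-BESTest.

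Sections 2.2 and 2.8 set the assessments, which under section 2.2 apply to all participants: "baseline (before starting the program), after three months, and upon completion of the program at six months".

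Section 2.7.1, within the description of the intervention, adds a second schedule. Progress is to be "monitored through functional ability tests, including the 2-min walk test, the five-times sit-to-stand test, etc", and "These tests will be conducted every three weeks to assess participants’ functional abilities and overall improvement". On the results, "the intensity and content of the exercise program will be adjusted accordingly". Section 2.9 describes the control arm as usual care plus an activity-tracking app and mentions no interim testing.

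For nutrition, section 2.5 lists three tools for judging the effectiveness of the education sessions. One of them is tied to those sessions: "After each biweekly nutrition education session, participants are asked to complete a 12-item questionnaire".

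**The concern.** Performance on a timed or paced test can improve with repetition alone, as people learn the task and how to pace it. If one arm repeats the outcome tests several times more often than the other, the between-group difference at month 6 combines a change in function with a difference in familiarity. The extra exposure coincides with allocation, so on these two tests no covariate, imputation model or per-protocol set can separate the two parts. Blinding the assessors (section 2.10) does not act on practice. At stake is how far a better two-minute walk or sit-to-stand result can be read as better function.

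The 12-item questionnaire raises a different issue, which is one-sided measurement rather than practice. Controls attend no nutrition sessions, so under the stated rule they never complete it.

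**Working it through.** **Who takes the tests.** The article never says outright that controls are not tested every three weeks. Three facts point the same way:

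- The three-weekly tests are described only under the intervention (2.7.1).
- Their results adjust an exercise program that controls do not receive.
- The usual-care section (2.9) lists no such tests, and the schedule common to all participants (2.2, 2.8) has three time points.

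**Exposures before each assessment.** The three-weekly checks fall at weeks 3, 6, 9, 12, 15, 18, 21 and 24. The article gives months, so six months is taken as 24 or 26 weeks. The preliminary familiarization session (2.2) is common to both arms and is not counted.

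| | Control | Be Cool |
|---|---|---|
| Before month 3, 24-week count | 1 (baseline) | 1 + 3 (weeks 3, 6, 9) = 4 |
| Before month 3, 26-week count | 1 | 1 + 4 (weeks 3 to 12) = 5 |
| Before month 6, 24-week count | 2 (baseline, month 3) | 2 + 6 = 8 if the week-12 check is the month-3 visit; 2 + 7 = 9 if separate |
| Before month 6, 26-week count | 2 | 2 + 8 = 10 |

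The excess before month 6 is 6 to 8 exposures per test.

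**What such an imbalance could do (assumption only).** The documents give no practice effect, so take an artefact d of 0.1, 0.2 or 0.3 SD, no true effect, 15 per arm (section 3.1) and a two-sided 0.05 test. The chance of a significant result comes from the noncentral t distribution with noncentrality d/SE.

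- Baseline-adjusted, assumed correlation 0.5: residual variance 1 − 0.5² = 0.75; SE = √(2 × 0.75/15) = 0.316 SD; 27 df. Noncentrality 0.32, 0.63, 0.95 gives 0.061, 0.094, 0.150.
- Unadjusted: SE = √(2/15) = 0.365 SD; 28 df. Noncentrality 0.27, 0.55, 0.82 gives 0.058, 0.083, 0.125.

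The sample size of 15 per group is used only as an input. The point does not depend on how it was derived.

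**Monitoring schedule.** Section 2.7.1 adjusts the program on three-weekly tests. Section 2.8 gives monitoring and program adjustment as the purpose of the three assessments. The two statements are not aligned.

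**The 12-item questionnaire.** It is completed after nutrition sessions, so there are no control data, and the first form follows the first session, so there is no pre-session baseline. The form covers the preceding week, so the first one may largely reflect habits before that session. The 7-day food diary and the food frequency questionnaire (FFQ) are not tied to sessions in this way.

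**The case against.** The strongest reply has four parts.

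- **Familiarization.** Every participant attends a preliminary session to become familiar with the procedures (2.2), which is a sensible step against early learning. This stands as mitigation, but it is shared by both arms and does not equalize 6 to 8 later exposures.
- **The package.** The trial compares a whole program with usual care, and regular testing with feedback is part of that program. This makes the matter a design trade-off rather than a plain mistake. The hypothesis, however, concerns functional ability, and skill at a test is not the same thing.
- **Size.** No practice effect is documented, and at 0.1 SD the error rate is barely above nominal. This stands: the mechanism is established, but a material bias is not.
- **Nutrition.** A form completed after each session reads naturally as a within-program process measure, and the between-group nutrition comparison can rest on the diary and the FFQ. This also stands. What remains is that section 2.5 lists the form among the effectiveness tools without making that distinction.

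A reader might go further and infer that Be Cool participants are trained to the outcome tests, or that the functional outcome as a whole is beyond rescue. The documents support neither. Section 2.7.1 uses the tests to adjust the program, not as exercises. Three of the five battery tests are not named in the three-weekly checks, although the open-ended *etc.* leaves their status unclear.

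**Conclusion.** The point holds for the two-minute walk and the five-times sit-to-stand. As written, the plan gives Be Cool participants about 8 to 10 prior exposures to each test before month 6, against 2 for controls, so familiarity and pacing are confounded with treatment on these measures. This rests on the inference that controls have no three-weekly tests, which the text strongly supports but does not state.

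The size of any bias is unknown. The error rates of about 6% to 15% (adjusted) or 6% to 12.5% (unadjusted) illustrate assumed artefacts of 0.1 to 0.3 SD and are not estimates. It would be wrong to infer that the trial's main result is compromised, because the primary outcome is quality of life and is not directly affected. This is a change that should be made to protect the reading of a secondary outcome.

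The 12-item questionnaire is a separate, smaller point. As scheduled, it cannot support a between-group comparison.

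**What to change.** - In section 2.7.1, replace *etc.* with a closed list of the tests used in the three-weekly checks. Keep the T25-FW, Berg Balance Scale and Mini-BESTest off that list and for baseline, month 3 and month 6 in both arms.
- Base the between-group functional conclusion on those three tests. Report the two-minute walk and sit-to-stand comparisons as supportive, with the unequal exposure stated. The cost is that two tests carry less weight.
- State in section 2.9 whether controls have any interim functional testing.
- Reconcile sections 2.7.1 and 2.8 on when the program is adjusted. How exercise is progressed is for the investigators and is not at issue here.
- Either give the 12-item questionnaire to both arms at the three existing visits (cost: 12 extra items per visit), or label it a within-program process measure and rest the between-group nutrition comparison on the food diary and the FFQ.

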#### 2.7.2. Nutritional Evaluation and Education

Nutrition education within the intervention is based on evidence-based principles of maintaining a balanced diet to support the specific needs of individuals with the condition. The guidance provided by the nutritionist is tailored to each participant’s dietary requirements, taking into account factors such as their medical history, nutritional needs, and personal preferences. Changes in participants’ dietary habits and adherence to nutritional recommendations are measured through various methods. These may include dietary assessments such as food diaries or 24-h recall interviews to track participants’ food intake and identify any changes over time. Additionally, participants’ weight, body composition, and other relevant health markers may be monitored to assess the impact of dietary changes on their overall health and well-being. A nutritious recipe is uploaded to the platform weekly to further support participants in adopting healthy eating habits. These recipes not only provide practical guidance on preparing nutritious meals but also serve as a source of inspiration and motivation for participants to incorporate healthier food choices into their daily lives.

Overall, the nutrition education component of the intervention aims to empower participants with the knowledge and skills they need to make informed dietary choices and optimize their nutritional intake to support their condition and overall health. Regular meetings with the nutritionist and access to practical resources such as nutritious recipes enhance participants’ ability to adhere to dietary recommendations and achieve their nutritional goals.

#### 2.7.3. Psychological Intervention

In the psychological component of the intervention, group organization is carefully tailored to ensure participants benefit optimally from shared experiences and support. Led by a psychologist, weekly group meetings conducted via Microsoft Teams focus on addressing participants’ psychological well-being. These sessions utilize a combination of acceptance and commitment therapy (ACT) techniques rooted in the tradition of behavioural therapy. Group organization may be based on factors such as participant preference or similarity in MS symptoms and challenges. ACT emphasizes psychological flexibility as a critical process for improving mental health, with core components including cognitive defusion, acceptance, self as context, values clarification, and committed action. Additionally, participants receive supplementary psychoeducational reading material aimed at enhancing coping strategies for managing MS challenges. This material provides valuable insights and practical tools to help participants manage MS more effectively. By integrating group therapy sessions with ACT techniques and psychoeducational resources, participants are equipped with a comprehensive toolkit to manage MS symptoms, negotiate challenges, and improve their overall quality of life [28].

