### 2.1. Eligibility Criteria

Prospective participants are eligible for the study if they meet the following criteria: they have a confirmed diagnosis of MS according to the McDonald criteria [20], exhibit the relapsing-remitting MS (RRMS) phenotype characterized by clearly defined attacks of new or increasing neurological symptoms, have experienced no relapses in the past six months, are between the ages of 20 and 60 years, have a confirmed diagnosis of MS for at least two years, and exhibit mild or moderate neurological disability, as defined by scoring between 0 to 5.5 on the Expanded Disability Status Scale (EDSS), indicating their ability to walk independently for at least 100 m without a cane [21].

The study will not include participants who have undergone psychotherapy in the past six months. Additionally, those with severe suicidality, including ideation, plan, and intent, or who have experienced one or more relapses in the previous month, have undergone corticosteroid treatment in the last month, have other severe medical conditions in addition to MS, or are currently pregnant, will not be able to participate in the study. After baseline testing, the principal investigator will perform randomization using sealed envelopes to allocate participants in a 1:1 ratio to either the BeCool or Control group.

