## 3. Data Analysis

### 3.1. Sample Size Calculation

Our study evaluates the effects of a holistic rehabilitation program on individuals with MS, utilizing key metrics to determine improvements in functional ability, nutritional status, and psychological well-being. Determining the minimum required sample size for our protocol was guided by preliminary data on quality of life [30]. Sample size calculations were performed using G*Power 3.0 [31], employing the “ANOVA: Repeated measures, within-between interaction” approach. This method facilitated estimating the study’s power to detect between-group differences and within-subject changes over time, considering three measurement points (baseline, mid-intervention, and post-intervention) for our MS participants. We set the statistical power and α error probability at 0.90 and 0.05, respectively, aligning with rigorous research standards to ensure sufficient sensitivity in detecting meaningful effects. Our calculations indicate that each group requires 15 individuals to power the study sufficiently. Analyses will adhere to the intention-to-treat principle, with multiple imputations used to handle missing data. A per-protocol and sensitivity analysis will also be conducted, excluding participants with significant non-compliance.

Detailed documentation and analysis of baseline demographics, including age, gender, disease duration, and relevant medical history, will provide valuable insights into the characteristics of our study population and allow us to control for potential confounding variables in our analyses. Additionally, thorough documentation of participants’ current disease-modifying therapy (DMT) regimens, including the type of medication, dosage, and duration of treatment, will enable us to assess the impact of DMT use on intervention outcomes and explore potential interactions with our intervention. We aim to conduct subgroup analyses to investigate differences in treatment effects based on baseline demographics and DMT use, with the goal of informing personalized approaches to MS management. By implementing these strategies, we aim to enhance the validity and generalizability of our findings and ultimately improve the care and outcomes of individuals living with MS.

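### The sample size makes no allowance for therapy-group clustering in the Be Cool arm, so the stated 0.90 power is too high for any positive within-group correlation

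*Protocol article*

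**What the plan says.** All references are to the protocol article.

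- **Randomisation (section 2.1).** Individuals are randomised; the plan is to "allocate participants in a 1:1 ratio to either the BeCool or Control group".
- **Group delivery (section 2.7.3).** Be Cool participants meet weekly in online groups led by a psychologist. Shared experience and mutual support are presented as part of how the component works. On composition: "Group organization may be based on factors such as participant preference or similarity in MS symptoms and challenges". The number and size of groups are not given.
- **Control (section 2.9).** Usual care; no therapy groups are described.
- **Sample size (section 3.1).** The procedure is "ANOVA: Repeated measures, within-between interaction" with three measurement points. "We set the statistical power and α error probability at 0.90 and 0.05, respectively". The result: "Our calculations indicate that each group requires 15 individuals to power the study sufficiently". No ICC, design effect or group size enters the account.
- **Primary outcome (Introduction).** Health-related quality of life, which section 2.7.3 expects the group sessions to improve.

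**The concern.** Individual randomisation makes participants independent at baseline. It does not keep them so once one arm is treated in groups. People who attend the same weekly sessions share a therapist, a discussion and each other's influence, and the protocol counts on that sharing. Any effect common to a group does not average out over its members, only over groups, and an arm of 15 is likely to have few groups.

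The named G*Power procedure has no term for this. Two things follow. The stated power is too high if the within-group correlation is positive. And if the final analysis uses the same independence model, its standard error for the arm difference is too small and its type I error exceeds 0.05. The first concerns a figure fixed in the article; the second depends on an analysis model that the article does not give.

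**Working it through.** **Inputs from the article:** alpha 0.05, power 0.90, two arms of 15 (N = 30), three time points.

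**Not in the article:** effect size f, correlation ρ between repeated measures, group size k, ICC. I assume k = 5 (three groups), 7.5 (two groups) or 15 (one group), and ICC 0.01, 0.05 or 0.10. The ICC is that of the outcome contrast being tested.

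**Step 1: the plan's own figure.** For the within-between interaction with sphericity, λ = N·3·f²/(1−ρ), df1 = 2 and df2 = 2(N−2) = 56. Power of 0.90 at N = 30 requires λ = 13.36. This is reached, for example, at f = 0.272 with ρ = 0.5 (90 × 0.272²/0.5 ≈ 13.3), at f = 0.244 with ρ = 0.6, or at f = 0.385 with ρ = 0. So 15 per arm is attainable but can be neither confirmed nor refuted. For what follows, only λ matters, and I take the nominal power to be exactly 0.90.

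**Step 2: clustering in one arm.** The Be Cool variance is multiplied by DE = 1 + (k−1)·ICC and the control variance by 1, so the variance of the arm difference is multiplied by V = (1 + DE)/2. Power is recomputed at λ/V. Example with k = 7.5 and ICC 0.05: DE = 1 + 6.5 × 0.05 = 1.325; V = 1.1625; λ/V = 13.36/1.1625 = 11.49; power 0.849.

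**Step 3: type I error if groups are ignored.** The unadjusted standard error is 1/√V of the true one, so the approximate error rate is 2·[1 − Φ(1.96/√V)].

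| Group size | ICC | DE | V | λ/V | Power | Type I error if ignored | Total N for 0.90 |
|---|---|---|---|---|---|---|---|
| 5 | 0.01 | 1.04 | 1.02 | 13.10 | 0.894 | 0.052 | 32 |
| 5 | 0.05 | 1.20 | 1.10 | 12.14 | 0.869 | 0.062 | 34 |
| 5 | 0.10 | 1.40 | 1.20 | 11.13 | 0.837 | 0.074 | 36 |
| 7.5 | 0.01 | 1.065 | 1.0325 | 12.94 | 0.890 | 0.054 | 32 |
| 7.5 | 0.05 | 1.325 | 1.1625 | 11.49 | 0.849 | 0.069 | 36 |
| 7.5 | 0.10 | 1.65 | 1.325 | 10.08 | 0.796 | 0.089 | 40 |
| 15 | 0.01 | 1.14 | 1.07 | 12.48 | 0.878 | 0.058 | 32 |
| 15 | 0.05 | 1.70 | 1.35 | 9.90 | 0.788 | 0.092 | 40 |
| 15 | 0.10 | 2.40 | 1.70 | 7.86 | 0.684 | 0.133 | 50 |

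At ICC = 0 nothing is lost. The power column is for a test that uses the correct variance. It ignores the further penalty for estimating that variance from few groups, so the losses are minimal ones. The last column holds group size fixed as N grows.

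**Step 4: cross-checks.** Simulation of an ANCOVA (20,000 runs) gave type I error at ICC 0.05 and 0.10 of 0.063 and 0.072 with three groups, 0.066 and 0.087 with two, and 0.092 and 0.134 with one. A two-arm calculation with 27 degrees of freedom, in place of the three-time-point interaction, gave power of 0.85 and 0.80 with two groups and 0.80 and 0.70 with one.

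**Step 5: does the way groups are formed matter?** In a second simulation (20,000 runs, groups of 5), the Be Cool arm was sorted into groups by baseline similarity with no shared group effect. Type I error was 4.9% and the SD of the arm difference 0.364, against 0.365 unsorted. With a shared effect at ICC 0.05 and 0.10, type I error was 6.3% and 7.2 to 7.5%, much the same whether sorted or not. The shared effect adds the variance; the sorting does not.

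**The case against.** The strongest reply is that every figure rests on an ICC and a group size that the article does not give. With groups of 5 and ICC 0.01 the loss is under one percentage point. Only one of four components is described as group therapy; exercise and nutrition are individually tailored and the cooling cap is worn individually, so a group effect on overall quality of life may be diluted. Fifteen per arm is also a stated minimum, not the enrolled number. All of this stands: the loss is conditional, and its size is a range.

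The single group of 15 is a bound, not the expected case. Preference or similarity can decide grouping only if there is more than one group, and four or five small groups would also fit the text.

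A reader might infer that forming groups by preference or similar symptoms is itself what inflates the variance, and that groups should be formed at random. This is not supported. Individuals are randomised, sorting them afterwards leaves the variance of the arm mean unchanged (step 5), the wording is only permissive, and composing groups to suit participants is a deliberate choice of delivery.

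A reader might also infer that the trial's standard errors will be too small. The article names repeated-measures ANOVA only for the sample size. The analysis model may stand in a statistical analysis plan that is not shown, so its absence is no fault. Type I inflation also needs group effects that exist yet average to zero; if the sessions affect no one, no shared effect arises.

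None of this rescues the power statement. It is made in the article, without allowance for group delivery, and a later analysis plan cannot change the basis on which 15 per arm was chosen.

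**Conclusion.** The point holds in a conditional form. Section 3.1 claims 0.90 power from a calculation that treats participants as independent, while one arm has a component delivered in groups and meant to work partly through sharing. For any positive ICC the claim is too high, unless the calculation had slack that is not shown. Taking nominal power as exactly 0.90, the loss is about 1 to 2 points at ICC 0.01. At ICC 0.05 to 0.10 it is about 3 to 6 points with three groups, 5 to 10 with two, and 11 to 22 with one. The ICCs and group sizes are assumptions.

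Only if the analysis follows the same independence model does the type I error rise, at ICC 0.05 to 0.10, to about 0.06 to 0.07 with three groups, 0.07 to 0.09 with two and 0.09 to 0.14 with one. The point is worth correcting, but it does not by itself invalidate the design.

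**What to change.** 1. In section 3.1, state the planned number and size of therapy groups, and give the power at ICC 0, 0.01, 0.05 and 0.10 under that plan.
2. Record each Be Cool participant's therapy group during delivery; it may be hard to reconstruct later.
3. As a sensitivity analysis, report the primary confidence interval with the Be Cool arm's variance multiplied by 1 + (k−1)·ICC at the same fixed values. This needs no estimate of the ICC.
4. Fit a partially nested model (group effect in the Be Cool arm only, small-sample degrees of freedom) only if there are enough groups to identify it. With two or three groups it is fragile.
5. If there is a single group, say plainly that its effect cannot be separated from that of treatment; no model can recover it.

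The way groups are composed can stay as it is. The cost is one recorded variable, a few sentences, a somewhat wider sensitivity interval and a less favourable stated power.
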